### Neurodevelopmental outcomes of VLBW infants and the role of mother’s own milk

Many VLBW infants show continued neurologic sequelae such as cognitive deficits, academic underachievement, grade failures and the need for remedial assistance during childhood and middle adolescence
[3]. Aside from intracranial lesions associated with preterm birth, factors shown to impact the neurodevelopmental outcome of VLBW infants include gestational age at birth, sepsis, necrotizing enterocolitis (NEC), chronic lung disease, suboptimal nutrient intake or poor growth
[2-8]. Compelling evidence exists to suggest that use of mother’s own breastmilk compared to infant formula during initial hospitalization positively affects the neurodevelopment of VLBW infants during early childhood and beyond
[9-15]. Vohr et al. demonstrated a dose dependent relationship between breastmilk intake for extremely low birth weight infants enrolled in the National Institute of Child Health and Human Development Glutamine Trial. For every 10 mL/kg/day increase in breastmilk intake, there was an associated increase in the Bayley Mental Development Index of 0.53 at 18 months corrected age (CA)
[14] which persisted to 30 months CA
[15]. The impact of this can be seen to be quite dramatic when comparing a baby who received no breastmilk to one who received 150 mL/kg/day which would equate to a difference of 7.5 points.

Mother’s own milk is thought to improve neurodevelopment because it is well tolerated by the VLBW infant, facilitating the transition from parenteral to enteral feeding, and due to its nutrient composition (with fortification as appropriate); both factors resulting in the provision of optimal substrate for brain development. Additionally, mother’s milk, via a myriad of bioactive components such as secretory IgA, lactoferrin and growth factors, protects from morbidities associated with preterm birth (NEC, sepsis, other infections) that are in turn additive risk factors for an adverse neurological outcome
[9,15,16].

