### Study objectives

The primary question is whether the use of pasteurized donor milk, compared to preterm formula, as a supplement to mother’s own milk for the first 90 days after randomization or until hospital discharge, whichever comes first, improves cognitive development of VLBW infants at 18 months corrected age as measured by the Bayley Scales of Infant Development, 3^rd^ edition (BSID). Secondary questions are whether donor milk will reduce a composite of death and serious morbidity (NEC, late onset sepsis, chronic lung disease and severe retinopathy of prematurity); support growth; and improve language and motor development at 18 months corrected age. Exploratory research questions include: will use of donor milk, as a supplement to mother’s own milk: (1) influence feeding tolerance and nutrient intake (2) have an acceptable cost effectiveness (medical and non medical) from comprehensive societal perspective?

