## Methods/Design

This is a pragmatic multi-centre, double-blind, RCT designed to evaluate the effectiveness of pasteurized donor milk as a supplement to mother’s own milk in those infants when mother’s own milk is unavailable. The analysis will be conducted using an “intention to treat” approach. Infants randomized to the intervention group received donor milk when mother’s own milk was unavailable. Infants randomized to the control group received formula designed for preterm infants when mother’s own milk was unavailable.

Funding was received from the Canadian Institutes for Health Research (MOP#210093), SickKids Foundation and the Ministry of Health and Longterm Care of Ontario. Infants were recruited in one of four participating level III NICU in Toronto and Hamilton, Canada. A comprehensive list of parental and infant demographic variables was collected after written informed consent was secured (Table 
3). Randomization, performed within 96 hours of birth, was done centrally using a 24 hr/day web-based third party randomization service (Centre for Mother Infant and Child Research, Toronto). The study allocation was randomly assigned in a ratio of 1:1, in random blocks of 4 and 8, with stratification by centre and birth weight grouping (<1000 g and 1000–1499 g). Aside from the research dietary technicians assigned to the study and a single neonatal dietitian, all members of the research study team (including outcome assessors), clinical teams and families are blinded to study allocation.

**Table 3 T3:** Demographic variables collected during the DoMINO trial

**Infant characteristics**	**Prenatal and parental characteristics**
Gestational age at birth+	Gravity/Parity*
Birth weight, length and head circumference+	Artificial reproductive technology (type and origin of eggs, sperm)+
Size for gestational age (small [SGA], appropriate [AGA] or large for [LGA] gestational age)+	Antibiotic use prior to delivery (prior 2 weeks)+
Sex+	Use of Prenatal Steroids+
Multiple birth status+	Cesarean delivery*
5-minute Apgar score+	Mom has previously breastfed (yes/no)*
Newborn Illness severity score (SNAP-II+)	Mom intends to breastfeed (yes/no)*
	Parental education (highest degree or diploma attained)*
	Parental weight and height (self-reported)*
	Parental age*
	Number of children in current household*
	Smoking (maternal history during pregnancy)*
	First language spoken in the home*
	Socioeconomic status (single parenting; above or below poverty line)*
	Ethnicity*

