### Statistical analyses

Using a 5 point difference in composite cognitive scores at 18 months CA, with 80% power (alpha level of 0.05), and an estimated standard deviation in each feeding group of 15, we estimated that we required 142 infants in each feeding arm. We assumed a 10% loss to follow-up during the feeding intervention and an additional 10% loss to follow-up after discharge, thus necessitating 176 infants to be randomized in each of the two feeding groups. As the number of infants withdrawn from the study exceeded 10%, primarily due to infant death, we overenrolled by 11 subjects to produce a final sample size of 363 subjects.

Analyses will be carried out using SAS Version 9.1 (SAS Institute, Cary, NC, USA). Descriptive statistics will be calculated for all variables of interest. Continuous measures will be summarized using means and standard deviations whereas categorical measures will be summarized using counts and percentages. The primary analysis for this intent-to-treat study will include all infants as randomized, regardless of adherence with the feeding protocol. The initial analysis will be a comparison of means (cognitive composite score) between the 2 groups at 18 months CA. A generalized linear model will carry out this comparison, controlling for length of treatment and adjusting for correlation of observations taken at the same centre. Sex, birth weight strata (<1000, 1000–1499 g), use of antenatal steroids, multiple birth, a count of key morbidities and duration of mother’s own milk-feeding are prognostic of neurodevelopmental outcome, and for this reason we will perform a secondary analysis which will include a regression model adjusted for the aforementioned characteristics
[4,6,13].

Children who cannot be tested on the BSID-III due to disability, severe delay or who perform below the threshold of the test for individual composite scores (cognitive, language motor) will be assigned a score of 49
[7]. The scores will be computed by trained individuals who have established inter rater reliability (R^2^ = 80) and who are blind to study group. Other missing data will be handled using methods of multiple imputation.

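### The adjusted secondary analysis includes a morbidity count that donor milk is hypothesised to change, so it does not estimate the total intention-to-treat effect

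*Protocol article*

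**What the plan says.** The Statistical analyses section of the protocol article describes two analyses of the cognitive composite score at 18 months corrected age. The initial one compares the two groups, controlling for length of treatment and allowing for correlation within centre. The secondary one is a regression adjusted for sex, birth-weight stratum, "use of antenatal steroids, multiple birth, a count of key morbidities and duration of" mother's own milk feeding. The only reason given for these covariates is that they are prognostic. Nothing labels the model as a mediation or direct-effect analysis.

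Other sections bear on the morbidity count:

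- **Study objectives.** A secondary question is whether donor milk reduces a "composite of death and serious morbidity (NEC, late onset sepsis, chronic lung disease and severe retinopathy of prematurity").
- **Background, on the role of mother's own milk.** Mother's milk "protects from morbidities associated with preterm birth (NEC, sepsis, other infections) that are in turn additive risk factors for an adverse neurological outcome".
- **Background, on donor milk.** A meta-analysis found more NEC with formula than with donor milk (relative risk 2.5, 95% CI 1.2 to 5.1). NEC is also linked there to adverse neurodevelopment.
- **Discussion.** The effect is expected to be possibly larger than 5 points, partly because smaller infants have more serious morbidity and so more room to benefit from human milk.

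**The concern.** Being prognostic is a sound reason to adjust for a variable that is fixed before treatment starts. It is not enough for a variable that treatment may change. A regression that holds morbidity constant compares donor-milk and formula infants who had the same number of morbidities. Any cognitive benefit gained by preventing a morbidity is then left out of the treatment coefficient.

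There is a second problem. Morbidity is also driven by how frail the infant is, and frailty affects cognition. If donor milk prevents some morbidities, infants with the same count in the two arms are no longer alike in frailty, and the comparison loses the protection of randomisation.

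What is at stake is interpretation. Without a label, a covariate-adjusted analysis may be taken as a refinement of the primary result. If the two differed, the gap could be put down to confounding when it was produced by the adjustment.

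**Working it through.** **Step 1: the planned effect.** The sample size takes its target from this statement: "Using a 5 point difference in composite cognitive scores at 18 months CA". The other inputs, from the same section, are 80% power, alpha 0.05 and a standard deviation of 15 per group.

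- Evaluable infants per arm, two-sided normal formula: 2 × (1.960 + 0.842)² × 15² / 5² = 141.3, rounded up to 142. This matches the plan: "we estimated that we required 142 infants in each feeding arm".
- Losses of 10% and then 10%: 142 / (0.9 × 0.9) = 175.3, rounded up to 176 per arm.
- Final total: 2 × 176 + 11 = 363.

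All three stated figures reproduce. None depends on the covariates at issue. The 5-point figure is the total effect that an adjusted model should also target.

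**Step 2: timing of the covariates.**

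| Item | When it is determined | Section |
|---|---|---|
| Randomisation | within 96 hours of birth | Methods/Design |
| Sex, birth-weight stratum, antenatal steroids, multiple birth | before randomisation | Table 3 and stratification |
| Late onset sepsis | more than 5 days after birth | Outcome measures |
| Chronic lung disease | 36 weeks postconception | Outcome measures |
| NEC, severe retinopathy | no time stated, but both are components of the trial's outcome composite | Outcome measures |
| Duration of mother's milk feeding | during the intervention and after discharge | Methods/Design |

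**Step 3: size under a linear model.** Adjusted effect = total effect − (reduction in mean morbidity count × points lost per morbidity). The documents give neither factor. The NEC relative risk cannot supply the first, because no baseline incidence is stated. Both are therefore assumed: a reduction of 0 to 0.3 and a cost of 3 to 7 points. With a total effect of 5 points, the adjusted effect is:

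| Reduction in mean count | 3 points each | 5 points each | 7 points each |
|---|---|---|---|
| 0 | 5.0 | 5.0 | 5.0 |
| 0.1 | 4.7 | 4.5 | 4.3 |
| 0.2 | 4.4 | 4.0 | 3.6 |
| 0.3 | 4.1 | 3.5 | 2.9 |

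The most that is removed is 0.3 × 7 = 2.1 points, or 2.1 / 5 = 42%. The least is zero.

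**Step 4: unmeasured frailty.** A simulation with two million infants per scenario used an assumed morbidity rate of 0.8 at average frailty and 5 points lost per morbidity. Frailty raised the morbidity rate in every scenario and, where shown, also lowered the score by 4 points per standard deviation.

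| Scenario | Effect without the count | Effect adjusted for the count |
|---|---|---|
| Rate lowered by 0.2; frailty does not affect the score | 5.1 | 4.0 |
| Rate lowered by 0.2; frailty lowers the score | 5.1 | 3.7 |
| Rate lowered by 0.3; frailty lowers the score | 5.1 | 3.0 |
| Rate lowered by 0.2; whole effect through morbidity; frailty lowers the score | 1.1 | −0.3 |
| Rate not changed; frailty lowers the score | 5.0 | 5.0 |

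The second row shows a further loss beyond the removed pathway. The fourth shows that the sign can reverse. The last shows that nothing happens if donor milk leaves morbidity unchanged.

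**The case against.** Several points on the other side stand.

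- **The list is not itemised.** The article does not say which morbidities are counted, and a condensed article may leave that to a fuller document. A morbidity present before randomisation would be a proper covariate. The point is therefore conditional, though the trial's own morbidity list is the natural reading.
- **Morbidity is one pathway, not the only one.** The Background first names better tolerance and nutrient composition. It states the protective effect for mother's own milk, and a later section says that pasteurisation reduces or destroys many protective components. The article nevertheless gives evidence that donor milk affects NEC, and it makes less morbidity a hypothesis of the trial.
- **Duration of mother's milk feeding is a weaker case.** A reader might treat it as equally harmful because it also follows randomisation. But both arms receive mother's milk first, families and clinical teams are blinded, and the article gives no reason for allocation to alter it.
- **The primary result is not touched.** A reader might infer that the main comparison is compromised. It includes neither covariate, and the article plainly calls the adjusted model secondary. (The primary model's control for length of treatment is a separate matter.)
- **Omitted baseline covariates are not an error.** A reader might fault the plan for leaving out gestational age, SNAP-II or parental education from Table 3. In a randomised comparison with a linear model, leaving them out costs precision only and does not bias the treatment effect.

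None of this supports adjusting for the morbidity count on prognostic grounds alone.

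**Conclusion.** The point holds for the morbidity count in the secondary model, provided that the count covers the trial's own morbidities. If donor milk works as the secondary hypothesis proposes, the adjusted coefficient is a partial direct effect that is also exposed to frailty bias. It should not be presented as a version of the intention-to-treat effect.

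The size is illustrative: 0 to 2.1 of 5 points under the assumed ranges. It would be wrong to conclude that attenuation of a given size will occur. It depends on an effect on morbidity that the trial has yet to test, and it is nil if there is none. Duration of mother's milk feeding is a lesser concern of the same type. The change should be made, but neither the primary comparison nor the sample size depends on it.

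**What to change.** - Restrict the adjusted secondary model to sex, birth-weight stratum, antenatal steroids and multiple birth.
- Remove the morbidity count. State which morbidities were meant; any that were present before randomisation may stay.
- Preferably remove duration of mother's milk feeding as well. The mother's intention to breastfeed, which Table 3 lists among the baseline variables, can stand in for it.
- If the pathway is of interest, report a morbidity-adjusted model separately, labelled as exploratory mediation, with its assumption of no unmeasured common cause of morbidity and cognition stated.
- Optionally, add gestational age, SNAP-II or parental education for precision.

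The cost is a change of wording in the analysis plan. The replacement variables are already collected, 142 evaluable and 176 randomised infants per arm stand, and the article reports that long-term follow-up was still underway.

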## Discussion

More than 2,700 VLBW(<1500 grams) babies are born in Canada each year with a length of hospital stay varying from 59 to 113 days compared to an average of 2–3 days for a healthy term infant
[85,86]. Although children born of VLBW represent a small proportion of children born in Canada, they represent an important cause of neurodevelopmental delay and disability in childhood and consume a disproportionately large amount of health care dollars
[3,85,87]. Interventions that can promote better health and development of these children can thus have a large impact. Although, in older trials, donor milk was protective against the development of NEC, there have been no studies to date assessing long-term outcome following donor milk supplementation in current era NICUs.

The societal implications of a 5 point difference in the cognitive composite score on the Bayley Scales of Infant and Toddler Development (BSID) are substantial
[15]. Currently, half of VLBW infants require special education services at school
[88-91], even among children without neurosensory impairment
[92] which has been shown to translate into a lower level of academic achievement in adulthood (e.g. number of high school graduates)
[93,94]. Vohr et al. argue that a 5 point difference could translate into a reduction in the number of children requiring special education services, associated costs, and improve long-term academic achievement
[15]. In a detailed analysis of the economic gains realized as a result of lowering environmental lead exposure in the U.S., Grosse et al. estimated that the 5 point improvement in cognitive scores realized amongst 1–5 year old children equates to a 9 to 12% increase in work productivity in adulthood
[83].

Anderson et al. previously showed a 5 point improvement in cognitive outcome in low birth weight infants fed mother’s own milk instead of formula
[9]. Given the VLBW infants in this RCT were considerably smaller than those in the Anderson meta-analysis, it is reasonable to assume our effect size may be larger as serious morbidity (e.g. NEC and sepsis), poor growth, and long-term neurodevelopmental sequelae are inversely related to gestation at birth
[2,3]; hence, there is a much greater opportunity for human milk to improve BSID-III scores.

The 90 day intervention period was chosen as at the time of initiation of this trial, the only available RCT on this research question reflective of current clinical practice also used a 90 day period

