[30]. This will facilitate a comparison of results from the two studies. Ninety days also reflected the average length of hospital stay of VLBW infants from the recruiting NICUs at the study initiation. The duration of the exposure is sufficient to observe differences in neurodevelopmental outcome at 18 months as Lucas et al. demonstrated differences in BSID scores at 18 months CA between infants (<1850 g) fed mother’s own milk versus formula for an average duration of 4 weeks during initial hospitalization
[74]. These differences translated into a higher IQ (8.3 points) at 7.5 years of age even after controlling for maternal education and social class (*p* < 0.0001).

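### The adjusted secondary model omits gestational age, which the protocol records and itself names as prognostic, and also omits recorded parental education

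*Protocol article*

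**What the plan says.** The Statistical analyses section describes two models for the 18-month cognitive composite.

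- **Primary comparison:** a generalized linear model "controlling for length of treatment and adjusting for correlation of observations taken at the same centre".
- **Adjusted secondary model:** the covariates are "Sex, birth weight strata (<1000, 1000–1499 g), use of antenatal steroids, multiple birth, a count of key morbidities and duration of mother’s own milk-feeding". The reason given is that these are prognostic of neurodevelopment, and so "we will perform a secondary analysis which will include a regression model adjusted for the aforementioned characteristics".

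Table 3 in Methods/Design lists what is collected at baseline. It includes "Gestational age at birth", from medical records, and "Parental education (highest degree or diploma attained", from parental interview.

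Elsewhere the article comments on both variables:

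- The Background subsection on neurodevelopmental outcomes says that "factors shown to impact the neurodevelopmental outcome of VLBW infants include gestational age at birth", with gestational age first in the list.
- The Discussion says that "long-term neurodevelopmental sequelae are inversely related to gestation at birth" and uses this to argue that the effect may exceed 5 points.
- The Discussion reports that an IQ difference in a cited feeding comparison held "even after controlling for maternal education and social class".

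**The concern.** The protocol gives a complete covariate list and the rule behind it, which is prognostic value. Gestational age meets that rule by the protocol's own account and is in the dataset, yet neither described model uses it. The only related term is birth weight in two levels. No family-background variable enters either model, although parental education is recorded and the protocol cites evidence in which maternal education was controlled.

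At stake is the quality of the adjusted estimate. A strong baseline predictor that is left out stays in the residual variance, and a chance difference between arms in that predictor is not corrected. Covariates added after unblinding would look data-driven, so the time to settle the list is now.

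**Working it through.** **1. The plan's own sample size reproduces.** Inputs from Statistical analyses: difference 5, SD 15, alpha 0.05 (taken as two-sided), power 80%.

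- n per arm = 2 × [15 × (1.960 + 0.842) / 5]² = 141.3, so 142, as stated.
- Two successive 10% losses: 142 / (0.9 × 0.9) = 175.3, so 176, as stated.
- Total: 2 × 176 + 11 = 363, as stated.

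This calculation uses the unadjusted SD and belongs to the primary comparison. Nothing below changes it.

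**2. The covariate list against the protocol's own statements.**

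| Variable | Recorded at baseline (Table 3) | Named in the text as affecting outcome | In the adjusted model |
|---|---|---|---|
| Gestational age | Yes | Yes, in Background and Discussion | No |
| Parental education | Yes | Indirectly: maternal education is a control in a cited comparison | No |
| Birth weight | Yes | Randomisation stratum, listed as prognostic | Yes, in two levels |

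**3. Gain in precision.** Let p be the share of the current adjusted model's residual variance that the added covariates explain. The documents give no value, so 5-20% is an assumption. The confidence interval width is multiplied by √(1 − p):

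| p | √(1 − p) | Narrowing |
|---|---|---|
| 0.05 | 0.975 | 2.5% |
| 0.10 | 0.949 | 5.1% |
| 0.15 | 0.922 | 7.8% |
| 0.20 | 0.894 | 10.6% |

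The range is therefore about 3-11%. It is given in relative terms because the residual SD of the six-covariate model is not stated.

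For scale only, with no covariates at all: SE = 15 × √(2/142) = 1.78 and the 95% half-width is 1.96 × 1.78 = 3.49 points. The present adjusted model should start below that, to the extent that its six covariates explain variance.

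**4. Chance imbalance.** The typical (1 SD) shift in the group difference from imbalance in the omitted covariates is √p × SE. With the unadjusted SE of 1.78, an upper figure for this model:

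- p = 0.05: 0.224 × 1.78 = 0.40 points
- p = 0.20: 0.447 × 1.78 = 0.80 points

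The target difference is 5 points.

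**5. Cost in degrees of freedom.** With 284 evaluable infants, an intercept, a treatment term and six single-term covariates leave 284 − 8 = 276 residual degrees of freedom (centre ignored). One uninformative extra term widens the interval by a factor of about √(276/275) = 1.002, or 0.2%.

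**The case against.** Several points on the other side stand.

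- **The model is secondary.** The trial's main result does not depend on it.
- **Gestational age is partly represented.** Birth-weight stratum is in the model and was a stratification factor. How much gestational-age information two levels carry cannot be judged from the documents.
- **Covariate choice involves judgement.** The list cites supporting literature that is not available here, and a separate analysis plan may say more. This carries less weight for gestational age, because the mismatch lies between a stated rule and statements in the same article.

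Three stronger readings are tempting, and the documents do not support them.

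- **That the omission biases the treatment effect.** Omitting a baseline covariate from a linear model in a 1:1 randomised trial does not do so, and chance imbalance is already reflected in the standard error. Withdrawals exceeded 10%, mainly through death, so a difference in survival between arms could shift the gestational-age mix of the tested children. That is conditional: the article gives no deaths by arm.
- **That the protocol treats parental education as a key determinant.** It does not. Education is absent from the Background list of factors, and the only support is its use as a control in one cited comparison of mother's own milk with formula.
- **That power rises from 80% to about 84-86%.** Those values follow from an assumed 10-15% of variance applied to the unadjusted SD of 15. They treat the six existing covariates as explaining nothing, and the 80% belongs to the primary comparison, which this change leaves alone.

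**Conclusion.** The point holds as a low-cost improvement to a secondary analysis. For gestational age there is a real mismatch: the variables were chosen for being prognostic, and one that the protocol twice names as related to outcome, and records, was left out. For parental education the case is weaker and rests on sensible use of collected data, with indirect support in the text.

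The benefit is precision and protection against chance imbalance in the adjusted model: an interval about 3-11% narrower, if the added covariates explain 5-20% of its residual variance. That range is assumed. The planned 142 per arm, the 363 randomised and the 80% power of the primary comparison are unaffected.

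The morbidity count and the duration of mother's own milk feeding arise after randomisation. That is a separate question about the same model, and adding baseline covariates does not settle it.

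**What to change.** Before unblinding, extend the covariate list of the prespecified adjusted model:

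- add gestational age at birth as a continuous term, keeping the birth-weight stratum because it was a stratification factor;
- add parental education as a further baseline covariate, with its categories fixed in advance.

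If either is left out on purpose, state the reason. No sample-size or primary-model text needs to change.

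The cost is one degree of freedom for gestational age if entered linearly and one fewer than the number of categories for education, each worth about 0.2% of interval width if uninformative. Both variables are already in the baseline data collection, and the plan already provides for multiple imputation if some values are missing.
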